#### Secondary outcome measures

##### Resting-state EEG

Besides impaired PPI, resting-state EEG alterations are frequently reported in SSD and BD [[73], [74], [75], [76], [77]]. In this study, resting-state EEG recordings are conducted prior to drink ingestion and 30 min thereafter. Resting-state EEG will be recorded under first both eyes-open (gaze fixation on visual mark in front of participant) and second eyes-closed conditions, with each condition lasting 5 min. Participants are instructed to remain seated, maintain an upright posture, relax and minimize movement during the recording. We investigate power spectral differences, specifically increased slow oscillatory power (delta/theta) in the frontal regions.

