**FIGURE 1 fig1:**
[figure not shown]
Overview of measurements during study participation. Schematic overview of the 5-day study protocol. On day 1, baseline assessments include psychiatric symptom scales [Positive and Negative Syndrome Scale (PANSS), Young Mania Rating Scale (YMRS), Inventory of Depressive Symptomatology (IDS-C)], anthropometric measures, and the application of continuous glucose monitors (CGMs) and sweat sensors. On days 2 and 5 (test days A and B), participants ingest either the ketone ester (deltaG, dGK) or an isocaloric carbohydrate control drink (iCarb). These test days include neuroelectrophysiological recordings [resting state, prepulse inhibition (PPI), and the P3b event-related potential], cognitive tests [Trail-Making Test A/B (TMT-A/B), Digit Span Test (DST), and the 15-Word Test (15 WT)], and visual analog scales (VAS). Optional procedures include intravenous blood sampling (≤8 times) and indirect calorimetry. EEG, electroencephalography; EMG, electromyography.

The study is conducted in an academic hospital setting (Amsterdam UMC, the Netherlands), specifically within the early-episode psychosis ward and acute psychiatry ward of the department of psychiatry. As patients are already hospitalized for the treatment of their psychotic or bipolar episode, they can be closely monitored throughout the trial without requiring additional hospital visits. This minimizes the burden on patients and facilitates their participation in the study.

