##### Patient-experienced and reported outcomes

Participants are asked to rate their energy level (from very exhausted to very energetic), mood (from very depressed to very happy), and ability to focus (from very poor to very well) using Visual Analog Scale at 2 timepoints: before and 2 h after ingestion of the nutritional drink, on both test days. Subjective improvements in mood and energy have been reported during ketogenic interventions, including among individuals with psychosis and bipolar disorder [47]. The patient-experienced outcomes are intended to provide exploratory insight into participants’ subjective experience of KE administration.

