##### Immune, oxidative stress, and metabolic blood parameters

Participants may opt out of blood sampling. For those who consent, a venous cannula is inserted into a forearm vein at the start of each session to facilitate sequential blood draws without repeated venipunctures. Blood is collected at the following time points: before drink ingestion (baseline, T0), at 20-min intervals during the first hour after ingestion (T1–T3), and at 30-min intervals thereafter (T4–T7), with a maximum of 8 blood draws and 123 mL per session. At each timepoint, ∼15 mL of blood is drawn and distributed over 5 tubes: 1 for serum (5 mL), 1 for plasma isolation using heparin (5 mL), and 3 EDTA tubes, used, respectively, for ketone body determination (1 mL), acylcarnitine profiles (1 mL), and remaining plasma. For ketone body determination, the EDTA sample is immediately mixed (1:1 ratio) with perchloric acid and kept on ice to prevent conversion into and evaporation of acetone. In addition, a 3 mL Tempus Blood RNA tube is collected at 1 h (T3) after drink ingestion, for gene expression analysis using the metabolic and immune nCounter gene expression panels from Nanostring. Following collection, all blood samples are handled in accordance with standardized laboratory protocols. Processed supernatants and aliquots are subsequently stored at −80°C until further analysis.

Immune, oxidative stress, and metabolic markers are determined in serum, plasma, and deproteinized blood. Markers are chosen according to prior research findings. Inflammatory markers include IL-6 and IL-10, measured in plasma, and high-sensitivity C-reactive protein (and soluble intercellular adhesion molecule-1 in serum) [13,20,[85], [86], [87]]. Oxidative stress markers include glutathione S-transferase and superoxide dismutase and key enzymes in ROS regulation [88,89]. Metabolic markers include glucose, ketone bodies (BHB and AcAc), and acylcarnitine profile [90,91].

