### *Statistical analysis*

Comparisons regarding all outcome measures within patients (dGK condition compared with control drink condition) are performed using paired-samples *t* tests for normally distributed data (or Wilcoxon signed-rank test if parametric assumptions are not met). Group-level effects will be analyzed using a linear mixed effects model, with adjustment for confounding factors. A significance level of ≤0.05 will be used. Given the exploratory nature of this pilot study, no imputation analysis will be conducted in the case of missing data (except for missing EEG channels) and no correction for multiple testing will be applied.

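### The paired test fixed for all outcomes gives no stated role to the pre-drink values of resting EEG, VAS and blood markers; covariate adjustment would use them at little risk

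*Protocol article*

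**What the plan says.** Three secondary outcome families in the protocol article have a measurement before the drink on each test day.

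- **Resting-state EEG:** "resting-state EEG recordings are conducted prior to drink ingestion and 30 min thereafter". The Figure 1 legend places these recordings on days 2 and 5: "These test days include neuroelectrophysiological recordings".
- **Patient-reported VAS (energy, mood, focus):** rated "before and 2 h after ingestion of the nutritional drink, on both test days".
- **Blood markers:** the first sample is taken "before drink ingestion (baseline, T0"), and "a venous cannula is inserted into a forearm vein at the start of each session", so there is a T0 on each day. Sampling is optional: "Participants may opt out of blood sampling".

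The Statistical analysis section gives one rule for the drink comparison: "Comparisons regarding all outcome measures within patients (dGK condition compared with control drink condition) are performed using paired-samples" t tests, with the Wilcoxon signed-rank test as fallback. It does not say whether the value entered is the post-drink value or the change from pre-drink. A separate sentence assigns group-level effects to a linear mixed effects model adjusted for confounders, which it does not name. Neither sentence mentions the pre-drink values.

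**The concern.** A paired test takes one number per patient per condition. Resting EEG and VAS yield two, and blood up to eight. Within a paired test the pre-drink value can be used in only two ways: discard it, or subtract it. It cannot be a covariate.

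Pairing removes stable differences between patients. It does not remove a shift in a patient's state from day 2 to day 5. Such shifts are plausible here: these are inpatients in an episode, treatment may be adjusted during participation, and usual diet continues. The pre-drink values are the design's direct record of them. If pre- and post-drink day differences are correlated, ignoring the record leaves removable variance in the estimate. If they are weakly correlated, subtracting it adds variance. The pilot is meant to inform the power analysis of a later trial, so the estimator and its variance for these outcomes matter beyond this study.

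**Working it through.** **The plan's own figure.** The sample size is 12 SSD + 12 BD = 24, from a pilot rule of 12 per group. The article gives no effect size, SD, power or precision target, so there is no precision figure to reproduce.

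**Set-up.** For each patient let D_post and D_pre be the ketone-ester-day minus control-day differences in post-drink and pre-drink values. Assume equal variances and correlation r. The documents do not give r; the range 0 to 0.7 is assumed.

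**Variance of the drink effect, relative to a paired t test on post-drink values**

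- Raw change scores: 2(1 - r).
- Baseline-adjusted (intercept of D_post regressed on D_pre): (1 - r²)(1 + 1/(n - 3)). The second factor is the cost of estimating the slope: 1 + 1/21 = 1.048 at n = 24, and 1 + 1/9 = 1.111 at n = 12.

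| r | Change score, any n | Adjusted, n = 24 | Adjusted, n = 12 |
|---|---|---|---|
| 0 | 2.00 | 1.000 × 1.048 = 1.048 | 1.000 × 1.111 = 1.111 |
| 0.3 | 1.40 | 0.91 × 1.048 = 0.953 | 0.91 × 1.111 = 1.011 |
| 0.5 | 1.00 | 0.75 × 1.048 = 0.786 | 0.75 × 1.111 = 0.833 |
| 0.7 | 0.60 | 0.51 × 1.048 = 0.534 | 0.51 × 1.111 = 0.567 |

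**Interval width.** The ratio is the square root of the variance ratio times the ratio of t quantiles (n - 2 against n - 1 degrees of freedom). For the adjusted analysis it is 1.03, 0.98, 0.89 and 0.73 at n = 24, and 1.07, 1.02, 0.92 and 0.76 at n = 12. Setting it to 1 gives break-even at r of about 0.22 (n = 24) and 0.35 (n = 12).

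**Power.** Take the standardised effect at which the post-only test has 80% power (two-sided 0.05, sidedness assumed): 0.597 at n = 24 and 0.889 at n = 12. Noncentral t gives:

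| r | Change score, n = 24 | Adjusted, n = 24 | Adjusted, n = 12 |
|---|---|---|---|
| 0 | 51% | 78% | 75% |
| 0.3 | 66% | 82% | 79% |
| 0.5 | 80% | 88% | 86% |
| 0.7 | 95% | 97% | 96% |

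A simulation of 40,000 runs per setting agreed to within about one percentage point. These figures carry no period term; adding one costs a further degree of freedom.

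**What r means here.** It is not the ordinary same-day pre-post correlation. Split the total variance into patient, day-within-patient and residual parts. Patient effects cancel in both differences, so r = day / (day + residual). A raw same-day correlation of 0.8 therefore gives:

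- r = 0 if all of it is between patients (patient 0.8, day 0);
- r = 0.1/(0.1 + 0.2) = 0.33 with patient 0.7, day 0.1;
- r = 0.4/(0.4 + 0.2) = 0.67 with patient 0.4, day 0.4.

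A high raw correlation alone does not show that adjustment will pay.

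**The case against.** The strongest reply has four parts.

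**The article does not say the values go unused.** A reader might infer that the plan throws them away. The text does not support that. It leaves the analysed variable open, and a paired test on within-day change would fit its wording and use them. This stands. What can be said is that no role is stated, and that both uses open to a paired test are inferior to adjustment over part or most of the range of r.

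**A mixed model is planned, and could carry a pre-drink covariate.** True, so it would be wrong to say that a paired test is all the plan contains. But that model is described for group-level effects, apart from the within-patient drink comparison, and adjusts for unnamed confounders. With drink order randomised, a pre-drink value is a prognostic covariate rather than a confounder, so the wording does not naturally include it.

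**This is detail for a full protocol or analysis plan that is not shown.** That holds for how a covariate is parametrised. It holds less for the choice of test, which the article itself fixes for all outcomes.

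**The gain is not guaranteed.** This stands. A reader might infer a certain loss of 1 - (1 - r²), i.e. 25% at r = 0.5 and 49% at r = 0.7. Those figures omit the cost of estimating the slope and hide the range where adjustment loses: at n = 12 and r = 0.3 the adjusted interval is slightly wider (1.02).

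Two further inferences also fail. Nothing in the article shows that day-to-day variation is the main source of noise. Nor does a chance pre-drink difference bias the paired test: order is randomised, and that variation is already in its standard error.

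**Conclusion.** The point holds as an improvable analysis choice for secondary outcomes. The paired test prescribed for the drink comparison cannot use the pre-drink values of resting EEG, VAS and T0 blood except as raw change scores, and the article states no role for them.

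The trade-off favours adjustment. At n = 24 its worst case in the assumed range is about 5% more variance (2 points of power at r = 0), and its gain reaches about 47% less variance at r = 0.7. Raw change scores can cost 29 points (80% to 51%) at r = 0. For an analysis within one diagnosis (n = 12) the case is weaker, with break-even near r = 0.35.

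These sizes rest on equal pre- and post-drink variances, on the assumed r, and on no drink effect persisting into the day-5 pre-drink value, which the 72-hour washout is meant to secure. Because blood sampling is optional, its n may be below 24.

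The primary outcome is outside the point: prepulse inhibition is described only at 1 h after the drink. So is the gene expression sample, described only at T3.

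**What to change.** In the Statistical analysis section, state for resting EEG, VAS and the blood markers with a T0 sample that the drink effect is estimated by regressing each patient's post-drink difference between conditions on the corresponding pre-drink difference, with period in the model. The equivalent mixed model has drink, period, the day's pre-drink deviation from the patient's mean pre-drink value, and that patient mean. Say explicitly that raw change scores are not the primary analysis of these outcomes. An unadjusted paired comparison can be reported alongside. Outcomes without a described pre-drink value keep their present analysis. How the serial blood samples are summarised is a separate question and need not change for this.

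The cost is a sentence or two of wording, 1-2 degrees of freedom per outcome, and a slight loss of precision where r is low. No new data, visits or patient burden are involved. The change should be made before the randomisation key is revealed.

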##### P3B event-related potential

The P3B amplitude is a subcomponent of the P300 specific type of event-related potential, reflecting cognitive processes such as attention, working memory, and decision making. P3B amplitude is considered a state and trait marker in SSD [78]. Both SSD and BD are associated with reduced P3B amplitude and delayed latency [73,79], yet the potential effects of ketone bodies on P3B amplitude remain unexplored. P3B amplitude is often measured by providing a random visual or auditory oddball paradigm where participants respond to infrequent stimuli in a sequence of a frequently occurring (standard) stimulus [78]. During our P3B task, conducted ∼45 min after ingestion, 160 stimuli are presented in random order, with participants instructed to press a button upon detection of the “oddball” target (32 out of the 160 stimuli). The task is preceded by 10 practice trials. The standard (nontarget) stimulus consists of a 500 Hz pure tone, whereas the “oddball” target stimulus is 700 Hz, each with duration of 100 ms. Both stimuli are presented at an intensity of 80 dB, with a random interstimulus interval ranging from 1.2 to 1.5 s. Throughout the P3B task, brain activity is recorded using the same EEG equipment as mentioned above to capture neural responses (Fz, Cz, and Pz channels), following the presentation of these stimuli.

##### Cognitive outcome measures

Cognitive impairments in SSD and BD have been extensively studied, highlighting deficits in cognitive domains such as executive functioning and memory [80]. The effects of the study drink on cognitive functioning are assessed using 3 validated neuropsychological tests: the Trail-Making Tests, the Digit Span Test (DST), and the 15-Word Test (15 WT). Collectively, these tests assess attention, cognitive flexibility, executive functioning, working memory, and verbal memory. The Trail-Making Tests (TMT-A and TMT-B, 2007, Dutch translation; paper versions) measure visual-motor speed, attention, and cognitive flexibility, with TMT-B also reflecting executive functions such as task-shifting [81]. The DST, as part of the Wechsler Adult Intelligence Scale (fourth edition), evaluates auditory working memory capacity, both in terms of forward and backward digit recall, as well as cognitive control [82]. The 15 WT (a Dutch adaptation of the Rey Auditory Verbal Learning Test) assesses short- and long-term verbal memory through immediate recall, delayed recall, and recognition of previously presented words, providing a comprehensive measure of memory processes [83]. Parallel tests are used to minimize learning effects, which are otherwise compensated by the AB/BA crossover design of the study. Cognitive assessments take place ∼90 min after ingestion. Previous studies have reported improvements in working memory and executive functioning following a single administration of exogenous ketones, including both MCT and KE [36,84]. Based on this evidence, it is hypothesized that similar acute effects on cognitive performance may also be observable in the present clinical sample.

##### Patient-experienced and reported outcomes

Participants are asked to rate their energy level (from very exhausted to very energetic), mood (from very depressed to very happy), and ability to focus (from very poor to very well) using Visual Analog Scale at 2 timepoints: before and 2 h after ingestion of the nutritional drink, on both test days. Subjective improvements in mood and energy have been reported during ketogenic interventions, including among individuals with psychosis and bipolar disorder [47]. The patient-experienced outcomes are intended to provide exploratory insight into participants’ subjective experience of KE administration.

##### Immune, oxidative stress, and metabolic blood parameters

Participants may opt out of blood sampling. For those who consent, a venous cannula is inserted into a forearm vein at the start of each session to facilitate sequential blood draws without repeated venipunctures. Blood is collected at the following time points: before drink ingestion (baseline, T0), at 20-min intervals during the first hour after ingestion (T1–T3), and at 30-min intervals thereafter (T4–T7), with a maximum of 8 blood draws and 123 mL per session. At each timepoint, ∼15 mL of blood is drawn and distributed over 5 tubes: 1 for serum (5 mL), 1 for plasma isolation using heparin (5 mL), and 3 EDTA tubes, used, respectively, for ketone body determination (1 mL), acylcarnitine profiles (1 mL), and remaining plasma. For ketone body determination, the EDTA sample is immediately mixed (1:1 ratio) with perchloric acid and kept on ice to prevent conversion into and evaporation of acetone. In addition, a 3 mL Tempus Blood RNA tube is collected at 1 h (T3) after drink ingestion, for gene expression analysis using the metabolic and immune nCounter gene expression panels from Nanostring. Following collection, all blood samples are handled in accordance with standardized laboratory protocols. Processed supernatants and aliquots are subsequently stored at −80°C until further analysis.

Immune, oxidative stress, and metabolic markers are determined in serum, plasma, and deproteinized blood. Markers are chosen according to prior research findings. Inflammatory markers include IL-6 and IL-10, measured in plasma, and high-sensitivity C-reactive protein (and soluble intercellular adhesion molecule-1 in serum) [13,20,[85], [86], [87]]. Oxidative stress markers include glutathione S-transferase and superoxide dismutase and key enzymes in ROS regulation [88,89]. Metabolic markers include glucose, ketone bodies (BHB and AcAc), and acylcarnitine profile [90,91].

##### EnLiSense sweat sensor and continuous glucose monitor

Participants will wear a noninvasive sweat sensor (EnLiSense LLC) throughout the 5-day study period, enabling near-continuous multiplex monitoring of biomarkers in sweat. This study focuses on markers linked to circadian rhythms and inflammation. Studying circadian rhythms is challenging because of the invasive nature of frequent melatonin and cortisol sampling, the primary regulators of circadian rhythms [92]. The ability to continuously measure cortisol and melatonin levels could provide deeper insights into the circadian rhythms of patients with SSD and BD [93]. Moreover, evidence from in vivo studies suggests that the KD may influence circadian rhythms [94], and it has been hypothesized that improvements in the sleep-wake cycle could mediate the beneficial effects of ketone bodies in SSD and BD [95]. Furthermore, IL-6 and TNF-α will be measured, as these proinflammatory cytokines are often be elevated in patients with psychosis [13,87]. In an acute inflammation mouse model, KE prevents increased expression in the brain of proinflammatory cytokines involved in SSD (IL-6, TNF- α, and IL-1β) [20], suggesting KE could normalize levels of these cytokines in SSD/BD. Therefore, assessing whether these markers change following ketone drink consumption could provide valuable insights into its potential effects on inflammation.

Melatonin, cortisol, IL-6, and TNF-α are determined in saliva samples as a validation for the sweat sensor data (Ella Automated Immunoassay System, Bio-Techne). Saliva samples are collected at fixed time points daily: 07:00 (or when the participant wakes up), 11:00, 15:00, 21:00, and 23:00 (or before bedtime). Saliva is collected in Eppendorf tubes by passive drool method (BioSaliva collection aid). Saliva samples are stored at −80°C until further analysis.

Additionally, participants wear a continuous glucose monitor (CGM, Abbott Freestyle Libre 2) for the entire 5-day duration of the study to gain further into the effects of a KE on glucose levels [87,96].

##### Indirect calorimetry

Information on substrate utilization and energy metabolism is obtained through indirect calorimetry. Indirect calorimetry is an optional test procedure for study participants. This method involves measuring oxygen consumption and CO_2_ production using a ventilated hood system (Q-NRG, Cosmed), which allows for the automatic calculation of resting energy expenditure (REE) and the respiratory quotient (RQ). REE reflects the energy metabolism of the participant at rest. The RQ (the ratio of CO_2_ exhaled to O_2_ consumed) provides insights into whole-body substrate oxidation, including glucose, fat, and protein. Participants are required to remain still, but not sleep, beneath the ventilated hood system for ∼15 min, after which the REE is calculated. Substrate oxidation is calculated as previously described [97].

### Data collection and management

Researchers involved in the study have received expert training in conducting PANSS, YMRS, and IDS-C interviews, performing electrophysiological measurements, administering cognitive tests, applying sensors, and collecting blood and saliva samples. Each participant is assigned a unique code for data storage, handling, and analysis, which cannot be directly traced back to the individual. Access to the identification key is restricted to authorized personnel. Data collection forms are completed on paper and subsequently entered into the eCRF (Castor EDC). To ensure data quality, assessors are thoroughly trained in Good Clinical Practice. Paper forms, including signed informed consent documents, are securely stored in a locked filing cabinet. Digital data are saved in a secured folder with restricted access for research personnel. Data will be retained for 15 y following the study's conclusion. Anonymous, selected material and data are shared after study conclusion with collaborators at the University of Texas (Department of Bioengineering, Dallas, USA) and the University of Alberta (Department of Pediatric Cardiology, Edmonton, Alberta, Canada) through Material and Data Transfer Agreements. Anonymous EnLiSense sweat sensor data are shared with EnLiSense LLC through a Data Transfer Agreement. All shared data and samples remain coded to protect participant confidentiality. An independent monitor performs quality assurance.

